# A randomised phase II trial of Stereotactic Ablative Fractionated radiotherapy versus Radiosurgery for Oligometastatic Neoplasia to the lung (TROG 13.01 SAFRON II)

**DOI:** 10.1186/s12885-016-2227-z

**Published:** 2016-03-04

**Keywords:** SBRT, SABR, Metastases, Lung, Cost effectiveness, Quality of life

## Abstract

**Background:**

Stereotactic ablative body radiotherapy (SABR) is emerging as a non-invasive method for precision irradiation of lung tumours. However, the ideal dose/fractionation schedule is not yet known. The primary purpose of this study is to assess safety and efficacy profile of single and multi-fraction SABR in the context of pulmonary oligometastases.

**Methods/Design:**

The TROG 13.01/ALTG 13.001 clinical trial is a multicentre unblinded randomised phase II study. Eligible patients have up to three metastases to the lung from any non-haematological malignancy, each < 5 cm in size, non-central targets, and have all primary and extrathoracic disease controlled with local therapies. Patients are randomised 1:1 to a single fraction of 28Gy versus 48Gy in four fractions of SABR. The primary objective is to assess the safety of each treatment arm, with secondary objectives including assessment of quality of life, local efficacy, resource use and costs, overall and disease free survival and time to distant failure. Outcomes will be stratified by number of metastases and origin of the primary disease (colorectal versus non-colorectal primary). Planned substudies include an assessment of the impact of online e-Learning platforms for lung SABR and assessment of the effect of SABR fractionation on the immune responses. A total of 84 patients are required to complete the study.

**Discussion:**

Fractionation schedules have not yet been investigated in a randomised fashion in the setting of oligometastatic disease. Assuming the likelihood of similar clinical efficacy in both arms, the present study design allows for exploration of the hypothesis that cost implications of managing potentially increased toxicities from single fraction SABR will be outweighed by costs associated with delivering multiple-fraction SABR.

**Trials registration:**

ACTRN12613001157763, registered 17th October 2013

## Background

SABR is emerging as a non-invasive method for precision irradiation of pulmonary oligometastases using radioablative doses with a higher biological effect than can be achieved with conventional radiotherapy. The paradigm of aggressive local treatment with SABR for oligometastatic disease is well recognised [1–3]. Stereotactic body ‘radiosurgery’ (SRS) refers to the accurate delivery of a single precise, large and highly conformal SABR treatment. Multi-fraction SABR and single fraction SABR represent a radical departure from classical fractionated radiotherapy. A previous systematic review [4] of SABR for secondary lung cancers performed in 2010 revealed 154 patients treated with single fraction SABR and 343 patients treated with fractionated SABR. In the single fraction experience, the mean weighted 2 year local control was 78.6 % (range 48–91 %) and 2 year overall survival was 50.3 % (range, 33–73 %). The rate of significant toxicity (grade 3 or higher) was only 3.3 %. The results are comparable in the fractionated SABR series. The 2-year weighted local control was 77.9 % (range, 67–96 %). The corresponding 2-year weighted overall survival was 53.7 % (range 33–89 %), with a 4 % rate of grade 3 or higher radiation toxicities. These outcomes are comparable with surgical alternatives, with low rates of significant toxicity.

Stereotactic radiotherapy is a rapidly evolving technique that has been implemented widely through Europe, North America and Japan. A survey of 1600 American radiation oncologists showed that 64 % of physicians used SABR (95 % confidence interval, 60–68 %), of whom nearly half adopted it in 2008 or later [5]. Lung was the most popular site of SABR use (89 %), with the three and four fraction SABR schemes accounting for 68 % of prescribed treatments. In contradistinction the single fraction approach is commonly employed by several institutions in Europe [6–10]. Similarly in the Australian context several dose-fractionation schedules have been developed. For example the Peter MacCallum Cancer Centre in Victoria has reported the use of a single fraction technique [11], whereas the Northern Sydney Cancer Centre have implemented a four fraction SABR approach in New South Wales. A retrospective comparison of these two approaches indicated no significant differences in clinical outcomes between single or multi-fraction approaches [12].

The primary purpose of this study is to compare single versus multi-fraction SABR in the context of pulmonary oligometastases. The proposed investigational fractionation schedules in the SAFRON phase II study are 28Gy in one fraction versus 48Gy in four fractions of SABR. Both fractionation schedules have been previously used in the context of lung metastases [4]. Comparing these arms using the biological effective dose (BED) calculation [13], it is apparent that these fractionation schedules are very similar for tumour effects (Table 1). Both arms deliver biological effective doses above 100Gy to the periphery of the target, which is known to correlate with very high rates of local control in the order of ~90 % [6, 10, 14]. A single fraction SABR is theoretically as effective as four-fraction SABR and is more convenient for the patient and has the potential to be more cost-effective. However the BED calculations (Table 1) suggest that there is a potential for greater late tissue toxicity from this approach. Theoretically, much of this potential toxicity is mitigated by highly accurate radiation delivery; nevertheless, there is clear clinical and theoretical equipoise to support the design of this trial.

**Table 1 Tab1:** BED calculations

	Arm (1): 28Gy in 1#	Arm (2): 48Gy in 4#
*Early (tumour) effects α/β = 10*	106Gy	105Gy
*Late (tissue) effects α/β = 3*	289Gy	240Gy

## Methods/Design

### Study design

This study is lead by the TransTasman Radiation Oncology Group (TROG) in collaboration with the Australasian Lung Cancer Trials Group (ALTG). The TROG 13.01/ALTG 13.001 SAFRON II study is a multi-institutional randomised interventional phase II clinical trial. The study has ethics board approval from the Peter MacCallum Cancer Centre (HREC/14/PMCC/2), and is registered on www.clinicaltrials.gov (ID: NCT01965223). All participating centres will obtain ethical approval prior to study activation. The study population are patients with oligometastases (1–3 metastases) to the lung (from any non-haematological malignancy). The trial schema can be found in Fig. 1. The intervention for ARM 1 is single fraction SABR - 28Gy delivered in one fraction. The intervention for ARM 2 is multi-fraction SABR - 48Gy delivered in four fractions, delivered over 2 weeks, with each fraction on non-consecutive days. Table 2 outlines dose constraints. Follow-up clinical visits including surveillance CT scanning will occur 3 monthly for year 1, 4 monthly for year 2, and thereafter 6 monthly until year 5 after treatment delivery. Written informed consent will be obtained from all individuals for participation in this study.

**Fig. 1 Fig1:**
[figure not shown]
Study flowchart

**Table 2 Tab2:** Normal tissue dose-volume constraints and standardised contouring nomenclature

Organ	Standardised name	Parameter	Investigational treatment	
		Constraint	28Gy in 1#	48Gy in 4#/2wks
Normal Lungs		V5 < 1000 cc	66 % 7.4Gy	66 % 12.4Gy, (max 3.1Gy per fraction)
Heart	Heart	Maximum dose (0.03 cc) < 15 cc	22Gy	34 Gy, (max 8.5 Gy per fraction)
			16Gy	28 Gy, (max 7 Gy per fraction)
Oesophagus	Oesophagus	Maximum dose (0.03 cc)	15.4Gy	30Gy, (max 7.5Gy per fraction)
Spinal Cord	SpinalCord	Maximum dose (0.03 cc)	12Gy	20.8Gy, (max 5.2Gy per fraction)
Brachial plexus	BrachialPlexus	Maximum dose (0.03 cc)	15Gy	24Gy, (max 6Gy per fraction)
Skin (5 mm subcutis)	Skin	Maximum dose (0.03 cc) < 10 cc	26Gy	36 Gy, (max 9 Gy per fraction)
			23Gy	33.2 Gy, (max 8.3 Gy per fraction)
Chest wall^a^	ChestWall	<70 cc	^b^26Gy to full thickness	30Gy
Great Vessels	GreatVessel	Maximum Dose (0.03 cc)	30 Gy	49 Gy, (max 12.25 Gy per fraction
Liver	Liver	V20, V30	No constraint, but dose/volume parameters to be documented	No constraint, but dose/volume parameters to be documented

^a^Chest wall dose limit may be exceeded if rib structure lies close to or in contact with the PTV

^b^26Gy isodose line should not cross full thickness of the chest wall structure

Definitions: Vx describes the volume that receives xGy, e.g. V5 < 66 % represents that the volume of specified OAR receiving 5 Gy shall be less than 66 %

The primary endpoint is safety of SABR treatment as measured by the incidence of grade 3 and 4 toxicities measured using CTCAE V4.0 within 12 months of treatment completion. Key secondary endpoints include a) Quality of life using EQ-5D and MDASI-LC, b) Local efficacy (time to local failure), c) Resource use and costs associated with treatment, d) Other clinical outcomes (overall survival, time to distant failure and disease free survival).

### Inclusion/exclusion criteria

Patients may be included in the trial only if they meet all of the following key inclusion criteria at randomisation:Aged 18 years or olderECOG 0–1 inclusiveA maximum of three metastases to the lung from any non-haematological malignancyIndividual tumour diameter ≤ 5 cm. Targets are located away from central structures (defined as 2 cm beyond bifurcation of lobar bronchi and central airways)o Note: Targets in proximity to chest wall and mediastinum that meet these inclusion criteria are eligiblePrimary and extrathoracic disease controlled with local therapy (e.g. surgery/definitive radiotherapy)

Key exclusion criteria are listed below:Previous high-dose thoracic radiotherapy in region of proposed SABR, as defined as a BED_10_ of 40GyCytotoxic chemotherapy within 3 weeks of commencement of or concurrently with treatmento Hormonal manipulation agents are allowable concurrently with treatment (e.g. aromatase inhibitors, selective oestrogen receptor modulators, and gonadotrophin releasing hormone receptor modulators)Concurrent targeted agents (such as sunitinib, bevacizumab and tarceva) are not allowedIt is recommended that targeted agents not be delivered within 7 days of delivery of radiation therapy treatmentGerm cell and small cell carcinoma histologies

### Statistical considerations

This study is a randomised controlled phase II multicentre trial, with the main objective to determine whether single fraction radiosurgery (28Gy/1) or fractionated SABR (48Gy/4) has acceptable toxicity for the treatment of pulmonary oligometastases, as defined by a maximum acceptable toxicity rate of grade 3 or higher adverse events of < 5 %.)

If both treatments have acceptable toxicity profile the criteria for selecting which arm will be used in the phase III trial is as follows:The arm with superior clinical outcomes will be chosen, based on time to local failure and overall survival.If there is no significant difference in clinical outcomes, the arm with the superior quality of life will be chosen.If there is no significant difference in quality of life, the arm associated with the least amount of resource use will be chosen.

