### Statistical analysis

Toxicities will be summarised as counts and percentages and presented in tabular form. The rate of grade 3 or higher toxicities at 1 year will be estimated for each arm by two methods. The first method (primary analysis) will evaluate the toxicities for participants who complete 1 year of follow up with 80 % confidence interval assuming binomial distribution. The second method (sensitivity analysis) will estimate the toxicities using cumulative incidences with death as a competing event. Time to event outcomes will be described using Kaplan-Meier methods with 95 % confidence intervals for each arm. The curves will be compared between arms using the Logrank test.

Overall Health-Related Quality of Life (HRQOL) will be measured using the MDASI-LC, a 22 item QoL module with three specific lung cancer questions. The results will be analysed using general linear mixed models. The area under the curve (AUC) will be compared between the arms using linear contrasts from the general linear mixed model. The linear mixed model will include arm, time and the interaction between arm and time as fixed effects with patients as random effect. Baseline MDASI-LC will be included as a covariate in the model. Completion rate of MDASI-LC at each time point will be reported in tabular form.

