### Sample size calculation

The maximum acceptable toxicity rate (grade 3 or higher adverse events) is considered to be 5 %. The desired upper limit of the 80 % confidence interval for a true toxicity rate of 5 % is 17 %. For a one-sided exact test for proportion with alpha = 0.1 and 80 % power, the required sample size is 38 evaluable patients for each arm of the trial. Assuming that up to 8 % of participants may be considered ineligible/unanalysable, 42 participants will be recruited in each arm.

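### Acceptable toxicity is defined as a rate below 5 %, but the 38 patients per arm are sized to rule out 17 %, so passing the sized test does not show the stated criterion

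*Protocol article*

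**What the plan says.** Three sections of the protocol article bear on the toxicity verdict.

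- **Statistical considerations** sets the main objective as deciding whether each schedule has acceptable toxicity, "as defined by a maximum acceptable toxicity rate of grade 3 or higher adverse events of < 5" %. It then makes the verdict a gate: "If both treatments have acceptable toxicity profile the criteria for selecting which arm will be used in the phase III trial is as follows".
- **Sample size calculation** repeats the threshold, "The maximum acceptable toxicity rate (grade 3 or higher adverse events) is considered to be 5" %, and adds a second figure: "The desired upper limit of the 80 % confidence interval for a true toxicity rate of 5 % is 17" %. The size follows: "For a one-sided exact test for proportion with alpha = 0.1 and 80 % power, the required sample size is 38 evaluable patients" for each arm. It does not say which rate is the null, which is the alternative, or in which direction the test runs. The allowance for loss is "Assuming that up to 8 % of participants may be considered ineligible/unanalysable, 42 participants will be recruited in each arm".
- **Statistical analysis** says the primary analysis "will evaluate the toxicities for participants who complete 1 year of follow up with 80 % confidence interval assuming binomial distribution". It gives no cut-off and does not name the binomial interval method.

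No sentence connects below 5 %, 5 % and 17 % in one decision rule.

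**The concern.** The objective says that an arm is acceptable if its rate is below 5 %. The sample size paragraph treats a true rate of 5 % as a case the design should tolerate, and 17 % as the upper limit that it wants to reach. These are different criteria. An arm can satisfy the second without giving good evidence for the first.

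The verdict is the primary conclusion for each arm, and the phase III choice depends on it. Under the definition in the objective, an arm that passes the sized test could be reported as having toxicity below 5 %, when the test has excluded only a rate more than three times as high (17/5 = 3.4). Because the direction of the test is not named, one possible result, 4 events in 38, also passes or fails depending on how the paragraph is read.

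**Working it through.** **Inputs.** From the Sample size calculation: rates of 5 % and 17 %, one-sided exact test, alpha 0.10, power 80 %, 38 evaluable per arm, 8 % loss. From the Statistical analysis section: an 80 % binomial interval, which leaves 10 % in each tail and so corresponds to one-sided alpha 0.10.

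**Formulas.** With X events in n patients, P(X ≤ c | n, p) = Σ C(n,k) p^k (1−p)^(n−k) over k = 0 to c. The exact (Clopper-Pearson) 80 % upper limit for x events is the p that solves P(X ≤ x | n, p) = 0.10.

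**1. Reproducing the 38: null p ≥ 17 %, alternative p = 5 %, accept if X ≤ c.**

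- Alpha at c = 3: P(X ≤ 3 | 38, 0.17) = 0.0008 + 0.0065 + 0.0248 + 0.0610 = 0.093. At c = 4 it is 0.2025, above 0.10, so the cut-off is 3.
- Power: P(X ≤ 3 | 38, 0.05) = 0.1424 + 0.2848 + 0.2773 + 0.1751 = 0.880.
- The first n to meet both criteria is 30, but power falls below 80 % again from 31 to 37. From 38 on it stays at or above 80 % (checked to n = 399).
- Recruitment: 38 / 0.92 = 41.3, so 42 per arm, as stated.

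The stated size is therefore reproduced by a test that rules out 17 %.

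**2. The opposite direction: null p ≤ 5 %, alternative p = 17 %, fail if X ≥ 5.**

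- Alpha: P(X ≥ 5 | 38, 0.05) = 0.040. Power: P(X ≥ 5 | 38, 0.17) = 0.7975, narrowly short of 80 %.
- This version accepts up to 4 events.

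**3. What each count shows at n = 38.**

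| Events | Observed rate | Exact 80 % upper limit | Rule out 17 % (step 1) | Not shown above 5 % (step 2) |
|---|---|---|---|---|
| 0 | 0 % | 5.9 % | pass | pass |
| 1 | 2.6 % | 9.9 % | pass | pass |
| 2 | 5.3 % | 13.4 % | pass | pass |
| 3 | 7.9 % | 16.7 % | pass | pass |
| 4 | 10.5 % | 19.9 % | fail | pass |
| 5 | 13.2 % | 23.1 % | fail | fail |

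The two directions disagree only at 4 events.

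**4. Can 38 patients exclude 5 %?** The most favourable result is 0/38. The exact one-sided p-value against 5 % is 0.95^38 = 0.142, above 0.10, and the upper limit is 1 − 0.10^(1/38) = 5.9 %. With all 42 evaluable, 0/42 gives 0.95^42 = 0.116 and 5.3 %. At least 45 evaluable patients without an event would be needed (0.95^45 = 0.0994).

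**5. Passing with a rate above the stated maximum.** At a true rate of 10 %, P(X ≤ 3 | 38, 0.10) = 0.465. The step 1 rule accepts such an arm 46 % of the time.

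**6. Sensitivity to the number evaluable.** The primary analysis counts only patients who complete one year, so n may not be 38. At n = 37, P(X ≤ 3 | 37, 0.17) = 0.105 exceeds 0.10, so the cut-off drops to 2 and power is P(X ≤ 2 | 37, 0.05) = 0.718. From 38 to 44 the cut-off stays at 3.

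**The case against.** The strongest reply is that the sizing, the test and the analysis already fit one reading. An 80 % interval matches one-sided alpha 0.10, and ruling out 17 % at a true 5 % meets the stated alpha and power at 38, while the opposite direction narrowly misses the power. Explicit hypotheses and an event count are also commonly left to the full protocol or analysis plan, which are not shown. Much of this stands. The size of 38 is sound, the 17 % reading is the better supported one, and the absence of an event-count rule from an article would be no finding by itself. It does not remove the mismatch: the article defines acceptability as below 5 %, and the reading that fits its sample size does not test that.

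A reader might infer stronger points that the document does not support.

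- *The observed rate must be below 5 %, so 2 or 3 events are also disputed.* No section says that the point estimate decides.
- *An observed rate near 5 % (2/38) has an upper limit of 13.4 %, so the 17 % is wrong.* The paragraph speaks of a true rate of 5 %. At that rate the exact limit is at or below 17 % with probability 0.88, which is consistent with sizing on power.
- *No analysis of 38 patients could ever exclude 5 %.* This holds for the exact test that the Sample size calculation names and for an exact 80 % interval. A Wilson 80 % interval for 0/38 ends at 4.1 %, and the Statistical analysis section does not name the method.
- *The design can rule out nothing lower than 17 %.* With 0, 1 or 2 events the exact limit is 5.9 %, 9.9 % or 13.4 %.
- *The 5 % is really the expected rate.* The article calls it the maximum acceptable rate.

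**Conclusion.** The point holds as a mismatch within the visible text about the primary decision threshold. The stated criterion is a rate below 5 %; the test that reproduces the 38 patients rules out 17 %. An arm passes that test with an observed 7.9 %, and passes 46 % of the time with a true rate twice the stated maximum. The unnamed direction changes the verdict at 4/38.

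The conclusion rests on exact binomial calculations, 38 evaluable patients per arm, and the two rates in the Sample size calculation being the null and the alternative. It is not a finding that the trial is too small for the test it appears to use. A full protocol or analysis plan may hold an explicit rule, but that would not reconcile the two sections of the article.

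**What to change.** Reconcile the Statistical considerations, Statistical analysis and Sample size calculation sections into one decision rule. State the null, the alternative, the direction, the interval method, and the maximum number of events per arm for the number actually evaluable.

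If the trial team keeps the 17 % design, the rule that follows from the plan's own figures is at most 3 events in 38 to 44 evaluable patients and at most 2 in 31 to 37. Power at 37 (72 %) should be acknowledged. The conclusion for a passing arm should then say that a rate of 17 % or more is ruled out, not that toxicity is below 5 %.

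If the team instead wants to show a rate below 5 % with an exact test, 38 per arm cannot do it, and the size would have to be reconsidered. Which toxicity rate is acceptable is for the trial team to decide.

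Keeping the 17 % design costs only wording and a less favourable claim, with no added patients.

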### Statistical analysis

Toxicities will be summarised as counts and percentages and presented in tabular form. The rate of grade 3 or higher toxicities at 1 year will be estimated for each arm by two methods. The first method (primary analysis) will evaluate the toxicities for participants who complete 1 year of follow up with 80 % confidence interval assuming binomial distribution. The second method (sensitivity analysis) will estimate the toxicities using cumulative incidences with death as a competing event. Time to event outcomes will be described using Kaplan-Meier methods with 95 % confidence intervals for each arm. The curves will be compared between arms using the Logrank test.

Overall Health-Related Quality of Life (HRQOL) will be measured using the MDASI-LC, a 22 item QoL module with three specific lung cancer questions. The results will be analysed using general linear mixed models. The area under the curve (AUC) will be compared between the arms using linear contrasts from the general linear mixed model. The linear mixed model will include arm, time and the interaction between arm and time as fixed effects with patients as random effect. Baseline MDASI-LC will be included as a covariate in the model. Completion rate of MDASI-LC at each time point will be reported in tabular form.

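### The primary toxicity rate is computed only in participants who complete 1 year of follow-up, so fatal toxicity within the year can never count and other early events may be lost, with bias in either direction

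*Protocol article*

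**What the plan says.** The endpoint paragraph after Table 2 defines the primary endpoint as the "incidence of grade 3 and 4 toxicities measured using CTCAE V4.0 within 12 months of treatment completion".

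The Statistical analysis section then says: "The rate of grade 3 or higher toxicities at 1 year will be estimated for each arm by two methods". Of these, the main one reads: "The first method (primary analysis) will evaluate the toxicities for participants who complete 1 year of follow up". It is reported as a binomial proportion per arm, and the interval has 80 % confidence. The other reads: "The second method (sensitivity analysis) will estimate the toxicities using cumulative incidences with death as a competing event". Toxicities are also tabulated as counts and percentages.

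The Sample size calculation sets the tolerance: "The maximum acceptable toxicity rate (grade 3 or higher adverse events) is considered to be 5" %. It adds: "The desired upper limit of the 80 % confidence interval for a true toxicity rate of 5 % is 17" %. It asks for 38 evaluable patients per arm and recruits 42, allowing 8 % for patients who are ineligible or cannot be analysed.

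The Background reports, for single-fraction series, that "2 year overall survival was 50.3" % (range 33 to 73 %). For fractionated series it gives 53.7 % (range 33 to 89 %). Grade 3 or higher toxicity was 3.3 % and 4 % respectively.

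**The concern.** The primary set is defined by an outcome. A patient who has a grade 3 event at month 4 and dies at month 8 meets the endpoint definition but has not completed 1 year. That patient leaves both numerator and denominator, and no exception is stated for someone who has already had an event. A patient lost to follow-up after an event is removed in the same way. A death caused by treatment within the year cannot enter the primary estimate at all.

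Safety is the only primary question, and acceptable toxicity in both arms is the condition for applying the phase III selection criteria under Statistical considerations. Each arm is judged on its own rate, so the distortion can differ between arms if early mortality or late toxicity differs. Table 1 itself anticipates more late tissue effect with the single fraction.

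**Working it through.** **1. The plan's own sample size.** An exact binomial test of 17 % against 5 % that accepts at most 3 events in 38 has alpha 0.093 and power 0.880. In the other direction (5 % against 17 %, rejecting at 5 or more of 38) alpha is 0.040 and power 0.798. The 80 % Clopper-Pearson upper limit for 3/38 is 16.7 %, close to the stated 17 %. Allowing for losses, 38/0.92 = 41.3, rounded up to 42. The figures 38 and 42 reproduce and are not in dispute.

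**2. How many complete 1 year.** The article gives no one-year mortality. Assuming a constant hazard, one-year survival is the square root of two-year survival.

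| 2-year survival | 1-year mortality | Completers of 42 |
|---|---|---|
| 50.3 % | 1 − √0.503 = 29 % | 29.8 |
| 53.7 % | 1 − √0.537 = 27 % | 30.8 |
| 33 % (lowest quoted) | 43 % | 24.1 |
| 89 % (highest quoted) | 6 % | 39.6 |

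If evaluable means completing 1 year, the 8 % allowance would have to cover these deaths, and at the weighted averages it does not. The loss of power is small: with 30 completers the test of 5 % against 17 % (4 or more events) has 77.5 % power, against 79.8 % with 38.

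**3. Fatal toxicity.** One fatal toxicity among 42 treated patients adds 1/42 = 2.4 percentage points to the rate in all treated patients and nothing to the completer rate. This component is always biased downward.

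**4. Non-fatal toxicity.** Assume a constant toxicity hazard λ, a death hazard μ without toxicity, and a death hazard kμ after toxicity.

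- True 12-month cumulative incidence: F = λ/(λ+μ) × [1 − e^−(λ+μ)]
- Alive at 12 months, with toxicity: A = λ e^−kμ × (1 − e^−a)/a, where a = λ + μ − kμ
- Alive at 12 months, without toxicity: B = e^−(λ+μ)
- Rate in completers: A/(A+B)

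With 28 % one-year mortality without toxicity, μ = −ln 0.72 = 0.3285. For F = 10 %, λ = 0.1243 and B = 0.6358. For F = 5 %, λ = 0.0603 and B = 0.6778.

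| k | A (F = 10 %) | Completers, true 10 % | Completers, true 5 % |
|---|---|---|---|
| 1 | 0.0842 | 11.7 % | 5.9 % |
| 2 | 0.0715 | 10.1 % | 5.0 % |
| 3.1 | 0.0604 | 8.7 % | 4.3 % |
| 4.4 | 0.0501 | 7.3 % | 3.6 % |

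At k = 1 the bias is upward because a patient whose toxicity occurs during the year has less of the year left in which to die: 16 % of patients with toxicity die before month 12, against 29 % of the others. The bias changes sign at k of about 2.1 (true 10 %) or 2.0 (true 5 %). With 6 % mortality, completers show 10.3 % (k = 1) to 9.4 % (k = 4.4) for a true 10 %. With 43 % mortality they show 13.0 % to 6.1 %.

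**5. What this does to an arm's result (counts assumed, 80 % intervals).**

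- 42 treated, 4 die early, 2 events in completers and 2 in those who died: completers 2/38 = 5.3 % (1.4 to 13.4 %); all treated 4/42 = 9.5 % (4.2 to 18.1 %).
- 42 treated, 12 die early, 3 events in completers and 1 in those who died: completers 3/30 = 10.0 % (3.7 to 20.9 %); all treated 4/42, as above.

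The completer analysis looks more favourable in the first case and less favourable in the second.

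**The case against.** The strongest defence is that the competing-risk analysis is already prespecified and that toxicity counts are tabulated, so events before an early death will be visible. That stands as mitigation. It does not settle the matter, because the acceptability objective rests on the analysis named as primary.

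A second defence is that a condensed article may abbreviate the definition of evaluable, and that an 8 % allowance fits poorly with dropping every early death. That is possible, but the article itself names the primary population and states no exception.

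A reader might go further and infer that the rule always favours declaring an arm safe, or that it removes mainly the patients who were harmed. The documents support neither. Step 4 shows that the non-fatal component is biased upward unless toxicity at least roughly doubles the death hazard, and no figure in the article suggests how large that effect is. With reported grade 3 or higher toxicity of 3.3 to 4 % and about half of patients dead at 2 years, most early deaths cannot be attributed to toxicity, and no rate of fatal toxicity is given. A smaller denominator also widens the interval, which makes a low upper limit harder to reach.

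Nor should 17 % be read as a pass mark. It is a planning figure for a true rate of 5 %; acceptability is stated as below 5 %, with no rule on the upper limit.

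**Conclusion.** The point holds as a fault in the primary analysis: it conditions on a post-treatment outcome and does not estimate the stated endpoint. The exclusion of fatal toxicity within the year follows from the wording alone and is always downward. For the rest, neither direction nor size can be fixed from the document. Under constant hazards and 28 % mortality, a true 10 % could be reported as anything from 11.7 % to 7.3 %, and a true 5 % as 5.9 % to 3.6 %, as the death-hazard ratio after toxicity goes from 1 to 4.4. The 10 % base rate is illustrative and above the rates quoted in the Background. A shortfall to about 30 or 31 completers per arm is likely if the quoted average survival applies with a constant hazard, but across the quoted range it runs from 24 to 40, so it is a possibility and not a certainty.

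The grade wording adds to the problem. The endpoint paragraph names grades 3 and 4 only, while Statistical considerations, Statistical analysis and Sample size calculation all refer to grade 3 or higher. Whether a fatal toxicity is an endpoint event is therefore unclear even before the completer restriction is applied.

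**What to change.** Exchange the two methods.

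- **Primary:** 12-month cumulative incidence of grade 3 or higher toxicity in all eligible treated patients, per arm, with toxicity-free death as the competing event and an 80 % confidence interval. State that any qualifying event before death or loss to follow-up counts.
- **Sensitivity:** the binomial proportion in participants who complete 1 year.
- **Endpoint wording:** reconcile grades 3 and 4 with grade 3 or higher, so that fatal toxicity counts.
- **Evaluability:** say whether the 38 evaluable patients are treated patients or one-year completers. Under the revised primary analysis, early deaths no longer draw on the 8 % allowance.

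The cost is a change of wording in the protocol and analysis plan. Both analyses are already planned, and no further patients or data are needed. The simple binomial interval gives way to a cumulative-incidence interval, and the reported rate may move slightly in either direction.
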